## Abstract

**Background:**

More than 70% of patients with depression who see their doctors experience insomnia. Insomnia treatment is a very important link for depression treatment. Furthermore, antidepression treatment is also important for depression insomnia. In acupuncture, LU-7 (Lie Que) and KID-6 (Zhao Hai), which are two of the eight confluence points in meridian theory, are used as main points. An embedded needle technique is used, alternately, at two groups of points to consolidate the treatment effect. These two groups of points are BL-15 (Xin Shu) with BL-23 (Shen Shu) and BL-19 (Dan Shu) with N-HN-54 (An Mian). The effectiveness of these optimized acupuncture formulas is well proven in the practice by our senior acupuncturists in Guangdong Provincial Hospital of TCM. This study has been designed to examine whether this set of optimized clinical formulas is able to increase the clinical efficacy of depression insomnia treatment.

**Methods/design:**

In this randomized controlled multicenter trial, all the eligible participants are diagnosed with depression insomnia. All participants are randomly assigned to one of two groups in a ratio of 1:1 and receive either conventional acupuncture treatment or optimized acupuncture treatment. Patients are evaluated using the Pittsburgh Sleep Quality Index(PSQI)and the Hamilton rating scale(HAMD) for depression. The use of antidepression and hypnotics drugs is also considered. Results are obtained at the start of treatment, 1 and 2 months after treatment has begun, and at the end of treatment. The entire duration of the study will be approximately 36 months.

**Discussion:**

A high quality of trial methodologies is utilized in the study, and the results may provide better evidence for the effectiveness of acupuncture as a treatment for depression insomnia. The optimized acupuncture formula has potential benefits in increasing the efficacy of treating depression insomnia.

**Trial registration:**

The trial was registered in Chinese Clinical Trial Register (ChiCR-TRC-00000481) on 12 August 2009.

## Background

More than 20% of Chinese people with depression and depressive neurosis experience from depressive symptoms [1]. Depression is a mental disorder with various characteristics, including negative emotions, anxiety, agitation, low self-esteem, dizziness, and suicidal tendencies [2]. Excessive levels of disturbed sleep among patients form one of the core symptoms known to be related with depression [3,4]. The prevalence of patients with depression and insomnia varies from 70.0% to 84.7%. The Insomnia is likely to increase the risk of deterioration and recurrence of depression, heart disease, social functioning, and the risk of suicide. Moreover, insomnia reduces the quality of life of patients with depression [5,6]. Meanwhile, insomnia is one of the most-diagnosed symptoms of depression and can be a risk factor for intractable depression and a predictor of depression disorder recovery [7]. Therefore, for those patients with depression insomnia, insomnia cannot simply be addressed through the use pharmacological treatment or other therapies for insomnia or depression. Treatments for both are very important.

Acupuncture, as a typical traditional Chinese medicine (TCM), has been applied for thousands of years [8]. The rapid development of acupuncture both within and outside China over the last few decades has itself led to great innovations in practice. Many studies, including clinical reports and systematic reviews, have investigated the benefits and success of acupuncture in relieving symptoms for various acute and chronic diseases, while a large history of clinical practice demonstrates that acupuncture appears to have an irreplaceable effect in treating depression and its symptoms, when compared with modern medicine and its antidepressive treatment. However, methodological flaws in design undermine the validity of these studies [9-11]. For example, two systematic reviews by Smith in the Cochrane Collaboration show that the clinical evidence for acupuncture treatment of depression is relatively limited before 2003 and that the quality of the clinical trials has improved between 2003 and 2008. The curative effects of acupuncture for depression are impossible to confirm [12,13].

In view of these data,this randomized, controlled, multicenter study of depression insomnia patients aims to determine the effectiveness of traditional acupuncture techniques. The study will compare a conventional acupuncture treatment formula with an optimized acupuncture treatment formula. The conventional acupuncture treatment formula is based on a point selection established on the basis of the particular TCM pattern of depression. Depression in Chinese medicine is mainly due to liver Qi stagnation, giving rise to symptoms appearing to be mental disturbance. LI-4 (He Gu), LIV-3(Tai Chong), EX-HN-3 (Yin Tang), and GV-20 (Bai Hui) are the points of the conventional acupuncture treatment formula. In optimized acupuncture formulas, the two empirical points LU-7 (Lie Que) and KID-6 (Zhao Hai) are added to the conventional acupuncture treatment formula. The action of these two points is used to improve the sleep quality of patients. Meanwhile, an embedded needle technique has proved to be effective for chronic disease or for those diseases demanding a longer retention time. Therefore, the technique is used to extend the effective treatment period in optimized acupuncture formulas [14].

A measurement system for evaluating the progression of illness, such as sleep quality and stress levels, will be used to compare the exact effect of different acupuncture treatment formulas.

## Methods/design

### Trial objective

The objective of this trial is to evaluate the effectiveness of treating depression insomnia by comparing the effects of a conventional acupuncture treatment formula and an optimized acupuncture treatment formula.

### Hypothesis

Acupuncture is capable of reducing levels of depression, whether with a conventional treatment formula or an optimized treatment formula. Furthermore, optimized acupuncture is capable of reducing levels of depression insomnia, to a greater degree than conventional acupuncture formula. Meanwhile, the results of the optimized formula of acupuncture treatment for depression insomnia are supposed to increase the clinical efficacy of treating depression insomnia, improve the health-related life quality of depression insomnia patients, and moderate the consumption of drugs used in conventional treatment, eventually leading to significant social and economic benefits.

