### Design

This is a multicenter, randomized, controlled prospective study. Participants receive optimized acupuncture (treatment group), or conventional acupuncture (control group) in a 1:1 allocation ratio (Figure 1).

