#### Eligibility

Participants meeting the following criteria are included:

1. Patient meets the diagnostic criteria for depression in the Chinese Classification of Mental Disorders, 3rd edition [15].

2. Patient meets the chief diagnostic criteria for insomnia (Diagnostic and Statistical Manual of Mental Disorders, 4th edition [16].

3. The Hamilton rating scale for depression (HAMD) count should be more than 20 points but less than or equal to 35 points.

4. The total Pittsburgh Sleep Quality Index (PSQI)count should be 7 points or over.

5. Patient is conscious without aphasia and mental retardation and is able to understand the rating scales.

6. Patients must be aged at least 16 years and not more than 50 years, and may be male or female.

7. The course of disease is between 2 weeks and 2 years.

Participants meeting one or more of the following criteria are excluded:

1. The depression is caused by organic mental disorders, psychoactive drug substances, or non-addictive substances.

2. Patients are aged less than 16 years or more than 50 years.

3. Patient is unable to understand the rating scales.

4. Pregnant women, patients with unstable heart condition, liver, kidney, and hematopoietic system diseases, and those who fear acupuncture are excluded.

5. Patients who cannot cooperate with their doctors are excluded.

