#### Randomizations and procedures for setting

The study procedures, risks, benefits, and data management are clarified in detail before the patients are asked to give their informed consent. To achieve comparable groups for known and unknown risk factors, a simple randomization is performed. Both groups have equal numbers of participants. The eligible participants are divided into two groups; the control group (indicated as 1 in the CRF) and the treatment group (indicated as 2 in the CRF). These groups will receive the acupuncture prescription as basic treatment but the treatment group will also be treated using the acupuncture points and techniques especially for insomnia. After inputting the estimated sample size into PEMS version 3.1, a sequence number, seed number, center number, and allocation result will be obtained. The allocation to the treatment or control group will then be performed using sealed consecutively numbered envelopes prepared by the trial team. Since this is a multicenter trial, after the patient is registered, the practitioners are informed, by telephone or other instant messenging, of the patient’s assignation to one of the two study formulas. This procedure ensures that the randomization is not influenced by the investigators taking part in this study. The practitioners participating in the study do not take part in the randomization process.

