### Data storage and statistical analysis of the trial outcomes

The data compilation form containing the variables of interest will be completed by the corresponding researcher at each center. Data will be documented in the paper CRF by researchers or evaluators and will be double-checked by quality inspectors. The supervisor will inspect the progress of the trial at regular intervals in each branch center. All the detailed original data (paper CRF) will be recorded timely, clearly, and completely. The case reports will be modified only by researchers who are documenting the data. The correct method of modification is tomark a line through the original record and write the revised data next to the original data,so that the change may be clearly visible. The modified data will be documented with data and the initials of the investigator. All the materials will be kept for 5 years after the completion of the study. At each center, the information obtained will be recorded on an electric database by EpiData software 3.1 at the same time, for subsequent statistical analysis.

Predictive Analytics Software (PASW, version18.0) is used for data analyses. Exploratory analysis will include the minimum, maximum, median, mean, and standard deviation. For measurement data, a normality test is necessary. Furthermore, baseline categorical data, demographic characteristics, such as sex and age category, and numerical data are analyzed with chi-squaretests and one-way analyses of variance (ANOVA). Student’s *t*tests are used tocompare different periods of measurement data. Wilcoxon matched-pairs signed-rank tests are used for ranked data. Independent Student’s *t*tests and 95% confidence intervals are used to detect differences between groups of the measurement data only if the normality test and analysis of variancetestsprove significant, otherwise rank-sum tests should be used, which are also used to detect differences between groups of ranked data. Linear mixed models (for continuous outcome variables) and generalized estimating equations (for categorical outcome variables) are used to examine changes over time and the severity of PSQI and HAMD. Both intention-to-treat and per-protocol analyses are used. Data from participants who do not violate the treatment protocols will be included in the per-protocol analysis. Missing data are dealt with using the ‘last value carried forward’ method.

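### The first hypothesis, that acupuncture under either formula reduces depression, cannot be tested by a trial in which both arms receive acupuncture

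*Protocol article*

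**What the plan says.** The Hypothesis section makes two separate statements. The first is absolute: "Acupuncture is capable of reducing levels of depression, whether with a conventional treatment formula or an optimized treatment formula". The second, introduced by the word Furthermore, is that the optimized formula does better than the conventional one for depression insomnia. The Background repeats the absolute aim, saying that the study "aims to determine the effectiveness of traditional acupuncture techniques", and its next sentence says that two formulas will be compared.

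The Design section gives two arms: "Participants receive optimized acupuncture (treatment group), or conventional acupuncture (control group) in a 1:1 allocation ratio". The randomization section adds "These groups will receive the acupuncture prescription as basic treatment", and under Study treatment the optimized formula is the conventional one plus extra points and embedded needles. No arm goes without acupuncture. The Trial objective is comparative only: the trial evaluates effectiveness "by comparing the effects of a conventional acupuncture treatment formula and an optimized acupuncture treatment formula". The sample size section sizes only a two-sided chi-square comparison of the two formulas.

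The statistical section plans Student's t tests that "are used tocompare different periods of measurement data", matched-pairs Wilcoxon tests for ranked data, and mixed models and generalized estimating equations for change over time. It also plans between-group tests.

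For entry, the HAMD "count should be more than 20 points but less than or equal to 35 points", the PSQI must be at least 7, and the illness may be as recent as 2 weeks. Antidepressants and hypnotics are recorded as a secondary outcome and are not among the exclusion criteria.

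**The concern.** A hypothesis that acupuncture reduces depression needs a comparison with what would have happened without acupuncture, and this trial has none. A reader who looks for the test of that hypothesis finds only before-after comparisons. In patients chosen for high scores on the outcome scale, some recently ill and some taking antidepressants, scores can fall for reasons unrelated to needling. If such a fall is reported with a p-value beside the first hypothesis, the trial will appear to show an effect that its design cannot identify. What is at stake is the conclusion the trial may draw about acupuncture itself, not its conclusion about the two formulas.

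**Working it through.** **1. The figure that the plan sizes.** The sample size section gives rates of 40% and 70%, 58 per group and 140 in total. Alpha and power are not stated; I assume 0.05 two-sided and 90%. With the pooled normal formula and mean rate 0.55:

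n = [1.960·√(2·0.55·0.45) + 1.282·√(0.40·0.60 + 0.70·0.30)]² / 0.30² = 55.7, so 56 per group.

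The stated 58 is close, and gives 91.2% power. This figure concerns optimized versus conventional only. Nothing is sized for an absolute effect.

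**2. What each comparison identifies.** Let A be the effect of the basic acupuncture prescription, B the added effect of the optimized formula, and S every non-specific change (natural recovery, drugs, regression to the mean).

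- Expected change in the conventional arm: A + S.
- Expected change in the optimized arm: A + B + S.
- Difference between the arms: B.

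S cancels in the difference, so B is identified. A appears only in the sum A + S, and no planned analysis separates the two. A mixed model does not help, because its contrasts are time (containing A + S) and formula (containing B).

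**3. Regression to the mean alone.** The article gives no HAMD mean, SD or test-retest correlation, so these are assumptions: SD σ = 6, correlation ρ = 0.6 to 0.8, source-population mean μ varied. Treat scores as normal, select those above 20 and up to 35, and set A = B = 0. Let m be the mean excess of selected scores over μ, and v their variance.

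- Expected fall = (1 − ρ)·m
- SD of change = √[(1 − ρ)²·v + σ²(1 − ρ²)]
- Noncentrality = fall·√58 / SD of change, for a paired t test with critical value 2.002 on 57 degrees of freedom

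Worked case, μ = 20, ρ = 0.7: m = 4.635 and v = 11.33. The fall is 0.3 × 4.635 = 1.39, and the SD of change is √(0.09 × 11.33 + 36 × 0.51) = 4.40. Noncentrality is 1.39 × 7.616 / 4.40 = 2.41. The probability of a significant fall is 66%.

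| Source mean | Expected fall (ρ 0.8 to 0.6) | P(significant fall) |
|---|---|---|
| 18 | 1.2 to 2.4 | 70% to 95% |
| 20 | 0.9 to 1.9 | 47% to 80% |
| 22 | 0.7 to 1.3 | 27% to 51% |
| 24 | 0.4 to 0.8 | 13% to 23% |
| 26 | 0.2 to 0.3 | 5% to 7% |
| 27.5 | 0 | 2.5% (nominal) |

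The effect vanishes at 27.5, the midpoint of the entry band, because selection is bounded above as well as below.

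**4. All non-specific change together.** Treatment is 24 sessions at two per week, so about 12 weeks. Assume a total non-specific fall of 3 points and an SD of change of 6 to 8. Noncentrality is 3 × 7.616 / 6 = 3.81 or 3 × 7.616 / 8 = 2.86, which gives 96% or 80%. A fall of 5 points gives more than 99% in both cases.

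**The case against.** The strongest reply is that the article already has the right objective. The Trial objective is purely comparative, the Background follows its broad aim with the between-formula comparison, and only that contrast is sized. The first sentence of the hypothesis could be read as a premise. This shows that the design suits its objective, but the hypothesis and the aim still say more than the objective does, and they should be brought into line with it.

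A reader might infer that the within-arm tests are the declared test of the first hypothesis and that a significant fall would be taken as confirmation. The article does not say so: no test is tied to that sentence and no rule for declaring it supported is given. What can be said is that no other planned analysis could bear on it.

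A reader might also infer that regression to the mean is bound to produce a significant fall. That is not supported either. The high probabilities need a source mean near the entry threshold, and the article gives no such mean. The article also lists data collection at baseline and at the start of treatment. If these are two separate pre-treatment measurements, regression to the mean could be reduced, but no such use is planned and natural recovery and drugs would remain.

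Finally, the randomized comparison is not biased by any of this, because these influences act on both arms alike. That stands in full.

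**Conclusion.** The point holds in a limited form. The first hypothesis and the broad aim in the Background cannot be answered by this design, whatever the data show. That rests on the arm structure and needs no numerical assumption.

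How often a within-arm test would mislead is assumption-based. With SD 6, correlation 0.6 to 0.8, 58 patients and no acupuncture effect, regression to the mean alone ranges from the nominal 2.5% to about 95%, depending on the source mean. With a total non-specific fall of 3 points it is 80% to 96%.

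A side point: the Hypothesis section also expects the optimized formula to "improve the health-related life quality of depression insomnia patients" and eventually to bring social and economic benefit. No listed outcome measures quality of life or cost. The wording reads as expected downstream benefit, not as an endpoint claim, so this is minor. Reduced drug use, named in the same sentence, does have an outcome.

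**What to change.** - Restate the hypothesis and the Background aim as the between-formula difference, in line with the Trial objective.
- Drop the statement that acupuncture reduces depression under either formula, or label it a background premise that the trial does not test.
- Report within-arm changes descriptively, as mean change with a 95% confidence interval, and draw no efficacy conclusion from them.
- Mark the quality-of-life and economic statements as expectations that the trial does not measure.

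No new data, patients or between-group analyses are needed, and the sample size is unchanged. The article says the project has concluded but the results are not yet published, so the change can still be made in the report. The cost is rewording and a narrower conclusion. A causal claim about acupuncture itself would need a concurrent comparator without it, which this trial does not have.

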### Design

This is a multicenter, randomized, controlled prospective study. Participants receive optimized acupuncture (treatment group), or conventional acupuncture (control group) in a 1:1 allocation ratio (Figure 1).

**Figure 1 F1:**
[figure not shown]
Flowchart for the study.

#### Eligibility

Participants meeting the following criteria are included:

1. Patient meets the diagnostic criteria for depression in the Chinese Classification of Mental Disorders, 3rd edition [15].

2. Patient meets the chief diagnostic criteria for insomnia (Diagnostic and Statistical Manual of Mental Disorders, 4th edition [16].

3. The Hamilton rating scale for depression (HAMD) count should be more than 20 points but less than or equal to 35 points.

4. The total Pittsburgh Sleep Quality Index (PSQI)count should be 7 points or over.

5. Patient is conscious without aphasia and mental retardation and is able to understand the rating scales.

6. Patients must be aged at least 16 years and not more than 50 years, and may be male or female.

7. The course of disease is between 2 weeks and 2 years.

Participants meeting one or more of the following criteria are excluded:

1. The depression is caused by organic mental disorders, psychoactive drug substances, or non-addictive substances.

2. Patients are aged less than 16 years or more than 50 years.

3. Patient is unable to understand the rating scales.

4. Pregnant women, patients with unstable heart condition, liver, kidney, and hematopoietic system diseases, and those who fear acupuncture are excluded.

5. Patients who cannot cooperate with their doctors are excluded.

#### Withdrawal criteria and management

Withdrawal or dropout criteria:

1. At the participants’ own request or that of the legal representative.

2. Participants who develop a serious disease, such as heart disease or pneumonia and, in the investigator’s opinion, it is not suitable to continue.

3. The participant’s compliance is poor, in the investigators’ opinion,and it is not suitable that they should keep taking part in the research.

4. The participants have an adverse reaction related with acupuncture treatment.

Withdrawn subjects or dropouts should be managed as follows. Details of the withdrawn patients should be documented in the ‘clinical trial performance forms’ in the case report files (CRF) of the patients. Details of patients who have withdrawn as a result of an adverse event or reaction should be recorded in the CRF. If the patients who have been determined as dropout or withdrawn cases require further treatment, the investigators should provide the treatments; however, their data will be treated as missing data.Details of all withdrawn patients will reported in the final results, to guarantee maximum transparency.

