#### Blind method

All eligible participants take part in a double-blind study. The participants in both groups are blinded. The evaluation of participants and analysis of results will be performed by professionals blinded to the assignation of treatment options. Those blinded professionals are required to conduct the outcome assessments, collect medication diaries, and check any missing data. Except for the practitioners, all of those involved in the outcome assessment are blinded to participant allocation.

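### Judged poor compliance ends follow-up as well as treatment, creating avoidable and possibly arm-related missing outcomes; the decider's blinding is not stated

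*Protocol article*

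**What the plan says.** All references are to the protocol article.

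- *Withdrawal criteria and management*, third ground: a patient leaves when "The participant’s compliance is poor, in the investigators’ opinion,and it is not suitable that they should keep taking part in the research". No attendance figure is attached. For withdrawn patients and dropouts in general, "their data will be treated as missing data". The section also promises that "Details of all withdrawn patients will reported in the final results, to guarantee maximum transparency".
- *Randomizations and procedures for setting*: the groups are "the control group (indicated as 1 in the CRF) and the treatment group (indicated as 2 in the CRF"), and after registration "the practitioners are informed, by telephone or other instant messenging, of the patient’s assignation to one of the two study formulas".
- *Blind method*: "Except for the practitioners, all of those involved in the outcome assessment are blinded to participant allocation". Participants, evaluators and analysts are blinded. Investigators who judge compliance are not mentioned either way.
- *Study treatment*: both arms have 24 sessions, two per week. Only the optimized arm also has embedded needles, which stay in until the next session.
- *Data storage and statistical analysis of the trial outcomes*: "Data will be documented in the paper CRF by researchers or evaluators". Intention-to-treat and per-protocol analyses are both planned, with gaps filled by last value carried forward. For the second set, "Data from participants who do not violate the treatment protocols will be included in the per-protocol analysis".

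**The concern.** The criterion joins two separate things: a patient not keeping to treatment, and a patient no longer being measured. Intention-to-treat analysis relies on keeping them apart, because it needs outcomes from patients whatever treatment they actually took. Under this rule the irregular attender leaves the research and the later scores are never collected.

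Two features could make the resulting gaps informative. First, the judgement is one of opinion, and nothing says it is made without knowledge of the arm. Second, adherence asks more of one arm than of the other, since only optimized-arm patients must tolerate needles between visits. Even an impartial judge could therefore remove patients at unequal rates.

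At stake is whether part of any difference between arms reflects who stayed under observation. The per-protocol set already separates treatment-protocol violators, so ending follow-up is not needed for that purpose.

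**Working it through.** **Inputs from the article.** 140 randomized 1:1, so 70 per arm; 40% success with the conventional formula; maximum dropout about 15%, and 0.15 × 70 = 10.5 per arm. **Assumptions.** No true difference (40% in both arms) and two-sided alpha of 0.05; the article states neither alpha nor power.

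**The article's own figures.** For 40% against 70%, at two-sided 0.05 and 90% power without continuity correction, 56 per arm are needed; the stated 58 gives 91.2%. Then 2 × 58 + 24 = 140, and 58/0.85 rounds up to 69 per arm, or 138. The stated size is reproduced closely and is not in dispute.

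**Step 1: extreme completer example.** Successes per arm are 0.40 × 70 = 28. Remove only non-responders, from one arm only:

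- 5 removed: 28/65 = 43.1%, a spurious gain of 3.1 points.
- 10 removed: 28/60 = 46.7%, a spurious gain of 6.7 points.

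**Step 2: milder cases.** Let w be the fraction of an arm withdrawn and s the share of withdrawals that are selected non-responders, the rest being random. Among those remaining, the observed success rate is p × [1 − w(1 − s)] / (1 − w), with p = 0.40. For example, w = 0.15 and s = 0.5 gives (0.40 × 0.925)/0.85 = 43.5%. The last column is the normal-approximation chance that a two-sided test rejects, with 70(1 − w) patients left per arm.

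| Withdrawn, control vs optimized | s | Control | Optimized | Difference | Rejection |
|---|---|---|---|---|---|
| 0% vs 15% | 1 | 40.0% | 47.1% | 7.1 | 12.7% |
| 0% vs 15% | 0.5 | 40.0% | 43.5% | 3.5 | 6.9% |
| 5% vs 15% | 1 | 42.1% | 47.1% | 5.0 | 8.6% |
| 5% vs 15% | 0.5 | 41.1% | 43.5% | 2.5 | 5.9% |
| 15% vs 15% | 1 | 47.1% | 47.1% | 0 | 5.0% |

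The distortion needs both unequal removal and selection on outcome.

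**Step 3: the same example under intention-to-treat with last value carried forward.** Removed non-responders stay in the denominator as failures: 28/70 against 28/70, a difference of 0.

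**Step 4: what carrying forward leaves behind.** The course is 24/2 = 12 weeks, with scores at the start, at 1 and 2 months, and at the end. A patient removed before the 1-month visit has only starting values, so shows no reduction. Suppose 5 or 10 patients in one arm are removed that early without regard to outcome. Of these, 0.40 × 5 = 2 or 0.40 × 10 = 4 would later have succeeded. That arm then shows 26/70 = 37.1% or 24/70 = 34.3% instead of 40%, a loss of 2.9 to 5.7 points. More removals in the optimized arm would then count against it, the reverse of Step 1.

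**Step 5: who knows the arm.** Practitioners are told the allocation. The CRF carries the group code, withdrawals are documented in the CRF, and evaluators, who are said to be blinded, may complete it. The article does not say which form shows the code or who sees it. The statements on the code, on blinding and on CRF completion need to be reconciled.

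**The case against.** The strongest reply is that intention-to-treat is planned, so a removed patient is not dropped from that analysis, and the 43% to 47% figures cannot be read as bias in it. That stands: Step 3 gives zero. The per-protocol set would exclude protocol violators in any case, and the illustration puts all removals in one arm, all among non-responders, using nearly the whole dropout allowance although there are four withdrawal grounds. That also stands, and the milder rows show how quickly the effect shrinks.

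A reader might infer that investigators remove patients knowing the arm. The article does not say so. It uses investigators and practitioners as separate terms and says only that practitioners are told the allocation. The supportable statement is that blinding of the decider is not stated.

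A session count may well be in the full protocol, so its absence from the article is not the point. What the article does state is that judged non-compliance ends participation and that the data then become missing.

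Reporting every withdrawal allows imbalance between arms to be examined, but it does not recover the lost scores.

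**Conclusion.** The point holds as a problem of avoidable and possibly informative missing outcomes. Its size is conditional. In a completer or per-protocol comparison the spurious gain is 3.1 to 6.7 points in the one-sided extreme (Step 1) and 2.5 to 3.5 points when half the removals are outcome-selected (Step 2). It is zero when removals are equal and equally selected. All of this assumes 70 per arm and 40% success in both arms. Under intention-to-treat with last value carried forward, the extreme example gives no difference. The remaining risk is outcomes frozen early, in an uncertain direction.

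Two stronger conclusions might be drawn and are not supported. One is that no handling of missing values could repair the problem: in the extreme example, counting the removed non-responders as failures restores a zero difference exactly. The other is that the criterion must be deleted outright: it also asks whether continuing is suitable, a judgement that an analysis set does not replace. Separating non-compliance with treatment from leaving follow-up is enough.

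**What to change.** State that poor compliance does not by itself end outcome follow-up. Record it as a protocol deviation against a fixed attendance count, applied by staff without the arm code and used only to define the per-protocol set. Continue PSQI and HAMD at the scheduled visits unless the patient withdraws consent, and use those values in the intention-to-treat analysis. Say whether the person judging compliance is blinded, and reconcile the statements on the CRF code. Report removals for poor compliance by arm. Any decision about continuing treatment stays with the investigators.

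The cost is a few sentences of protocol text and one per-protocol rule. The downside is that sites must keep inviting irregular attenders to assessments already planned. *Trial status* says the project concluded in 2011, so for this trial the remaining steps are to use any scores held after removal and to report these removals by arm, with their timing.
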